### Study components

Data collection will consist of three main components:
*Household surveys of malnutrition risk factors*. To evaluate the impact of the intervention on known malnutrition risk factors two detailed household surveys will be implemented, the baseline survey will be undertaken before the intervention begins and the endline one 3–4 months after the start of the intervention.Based on our working assumption that insecurity in the field will constrain the possibility of following-up the baseline sample, the surveys will select independent samples of households from the study clusters at the two periods. If security conditions are worse than anticipated and do not allow sampling within a sufficient number of clusters, then we will collect data from a single control and intervention cluster and the data will be analysed as a before and after comparative cross-sectional study. Furthermore, if security conditions do not allow us to undertake repeated surveys in the same clusters, then we will undertake a single survey at the end of the intervention, and the data will be analysed as a cross-sectional study. However, if field conditions are better than anticipated, we will follow-up the baseline sample and the data will be analysed as a longitudinal cohort.The surveys will collect data at the household level and from all the children aged <5 years and their mothers/carers living in the selected households. The data collected in these surveys will comprise data on household demographics, household expenditure and income, assets, food security, diet diversity, coping strategies, morbidity, WASH, access to health care, and infant and young child feeding practices. The surveys will also collect anthropometric data from children to describe their nutritional status. However, this anthropometric data will not be used to assess the impact of the intervention due to sample size limitations (see below).
*A community surveillance system* will be set up to collect anthropometric data that will be used to evaluate whether the intervention reduces the risk of developing acute malnutrition. In this surveillance system, community health workers (CHW) will collect monthly mid-upper arm circumference (MUAC) measurements to detect the incidence of acute malnutrition in an exhaustive sample of children aged 6–59 months from both intervention and control clusters. Those identified as malnourished will be referred to nutrition centres for treatment.
*A process evaluation* will be conducted in order to better understand: the context in which the intervention was implemented; document how the intervention was implemented compared to how it was planned; explore the mechanism through which the intervention worked or failed to work, and investigate any unexpected outcomes. To achieve these objectives we will compile and analyse routine quantitative programme monitoring data and local health facility data on routine admissions and any disease outbreaks. We will also conduct qualitative data collection on IDP perceptions of malnutrition, risk factors, and the impact of cash transfers. Data will be collected using key informant interviews with community leaders, health staff and mothers and fathers, and focus group discussions with separate male and female groups of internally displaced people. These will explore how and why the interventions were effective, or not effective, in reducing child acute malnutrition.

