### Study setting and population

The study will be conducted in IDP camps located in Weydow area, Deyniile district, Mogadishu. Deyniile and Dharkenley, two of the 17 districts of Banaadir region, host the majority of IDP in Mogadishu, who are primarily from marginalised tribes or minority groups [13]. Concern Worldwide (hereafter Concern) has been implementing multi-sector development and humanitarian assistance programmes in this setting.

The IDP camps in Weydow area are privately run, spontaneous settlements that are often overcrowded, lack basic sanitation and health services, and face recurrent evictions. Morbidity (diarrhoea, pneumonia, and fever) estimates in these camps are high and may be a major driver for high global acute malnutrition (GAM) estimates [6]. During the wet seasons (Gu and Deyr, Apr-Jun and Oct-Dec, respectively), morbidity estimates are particularly high, mainly due to diarrhoea [6].

Most of the IDP were previously agro-pastoralists and riverine farmers that lived in the Bay, Bakool, and Shabelle regions [13]. Currently, their primary livelihoods sources are casual labour, petty trading, and humanitarian assistance received from local and international humanitarian organisations [6].

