### Study design

The study design is a non-randomised cluster controlled trial. Concern will implement a routine needs assessment exercise to identify vulnerable beneficiaries and on that basis select the camps that will receive the intervention. All households in the selected camps will be registered for the intervention. A non-randomised design was chosen as the best available approach in this setting because the intervention will be allocated based on vulnerability criteria.

The cluster unit in the trial will be an IDP camp and the intervention arm will include 10 IDP camps selected to receive the intervention. The reason that only 10 camps can be selected to receive the intervention is the limit in the donor funding that is available to provide services in this area. The control arm will include another 10 IDP camps, located adjacent to the intervention camps that will not receive the intervention. Routine programme data suggests small differences in vulnerability between camps. Households in both arms will benefit from the services provided by Concern, such as care from OTP and MCHN centres.

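### The security fallback to one camp per arm leaves no between-camp degrees of freedom and ties the intervention to camp-specific change, yet the between-arm test is not restricted for that case

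*Protocol article*

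**What the plan says.** Study components gives the surveys a causal purpose: "To evaluate the impact of the intervention on known malnutrition risk factors two detailed household surveys will be implemented". Under Study design, "the intervention arm will include 10 IDP camps selected to receive the intervention", and another 10 adjacent camps serve as controls. Allocation is not random: "the intervention will be allocated based on vulnerability criteria".

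Study components then sets two separate security contingencies.

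- **Too few camps.** The trigger is "If security conditions are worse than anticipated and do not allow sampling within a sufficient number of clusters". The response is: "we will collect data from a single control and intervention cluster and the data will be analysed as a before and after comparative" cross-sectional study. No number defines sufficiency.
- **No repeat survey in the same camps.** The response is: "we will undertake a single survey at the end of the intervention, and the data will be analysed as a cross-sectional study". This one is not tied to one camp per arm.

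Data analyses plans a difference-in-differences test between arms on the survey data and makes no exception for either contingency. It names the clustering-aware survey commands for prevalence estimates. Outcome measures lists mean individual dietary diversity score (IDDS) as one of two primary outcomes, and the second hypothesis concerns risk factors, so both depend on these surveys.

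**The concern.** With one camp in each arm, arm and camp are the same variable. Before-and-after data cancel whatever is constant about the two camps. They do not cancel what changes in one camp and not in the other, and such a change is fully confounded with the intervention. The setting makes such changes plausible: the camps are described as "spontaneous settlements that are often overcrowded, lack basic sanitation and health services, and face recurrent evictions", and Programme monitoring data plans to track other agencies' relief because it may influence nutrition. Measuring more children in the same two camps does not help, because the missing replication is between camps.

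The rule also loses information without need. If the number of accessible camps falls below the unstated minimum but exceeds one per arm, the wording still reduces the survey to one per arm.

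At stake are the co-primary IDDS result and the second hypothesis. A test on two camps could report an effect of cash that is only a local difference in change. The endline-only route has a different weakness: without a baseline, starting differences from vulnerability targeting cannot be separated from effects.

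**Working it through.** **Inputs from Sample size calculation and Study design.** Difference 0.6 IDDS units, SD 1.5, power 80%, alpha 0.05 (two-sided assumed), ICC 0.01, 10 camps per arm, stated result 120 children per arm.

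**Assumed, because the article gives no figure for the fallback.** All 120 children per arm and survey come from one camp (m = 120). CAC, the correlation of a camp's effect between the two surveys, runs from 0 (fully changing) to 1 (fully stable).

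**1. The stated 120 depends on about 10 camps per arm.**
- Without clustering: n0 = 2 × [1.5 × (1.960 + 0.842) / 0.6]² = 98.1.
- With 10 camps and normal quantiles: 98.1 × 0.99 / (1 − 98.1 × 0.01 / 10) = 107.7.
- With t quantiles on 18 df: n0 = 2 × [1.5 × (2.101 + 0.862) / 0.6]² = 109.7, then 109.7 × 0.99 / (1 − 109.7 × 0.01 / 10) = 122.0, close to 120.
- Power at 120 per arm (10 camps × 12 children) with t on 18 df is 79.4%.

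**2. Degrees of freedom.** Between camps within arm: 2 × (10 − 1) = 18 as planned, and 2 × (1 − 1) = 0 under the fallback. Camp-to-camp variation in change cannot be estimated, so no valid camp-level test exists. A cluster-robust variance does not rescue it: in a model with arm, period and their product, residuals sum to zero within each camp and period, so the estimate is zero by construction.

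**3. Rejection rate of a test that ignores camps.** The true variance of the difference-in-differences is 4 × SD² × [(1 − ICC)/m + ICC × (1 − CAC)], and the test uses about 4 × SD²/m. The ratio is V = (1 − ICC) + m × ICC × (1 − CAC), and the rejection rate under the null is 2 × [1 − Φ(1.96/√V)].

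| CAC | V at ICC 0.01, m = 120 | Rejects a true null |
|---|---|---|
| 0 | 0.99 + 1.20 = 2.19 | 18.5% |
| 0.5 | 0.99 + 0.60 = 1.59 | 12.0% |
| 0.8 | 0.99 + 0.24 = 1.23 | 7.7% |
| 0.9 | 0.99 + 0.12 = 1.11 | 6.3% |
| 1 | 0.99 | 4.9% |

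Simulation with 40,000 runs gave 18.5%, 12.0%, 7.7% and 5.2% for CAC 0, 0.5, 0.8 and 1.

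**4. Sensitivity.** At ICC 0.01 and CAC 0.5, the rate is 10.8% with 100 children per camp and 13.4% with 144. With m = 120 and an ICC of 0.02, which is not in the article, CAC 0, 0.5 and 0.8 give 28.6%, 18.4% and 10.5%.

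**5. More children do not remove the problem.** As m grows, the standard error approaches √[4 × 1.5² × 0.01 × (1 − CAC)]: 0.30 at CAC 0 and 0.21 at CAC 0.5, against a target difference of 0.6.

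**6. Endline-only fallback.** If all 20 camps are surveyed, 18 df remain and the design effect is 1 + 11 × 0.01 = 1.11. Even ignoring camps, the rate is 6.3%. The weakness there is the missing baseline, which these rates do not measure.

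**The case against.** **The contingency may never have arisen.** Study status says the surveys are complete, and the Discussion lists modifications without mentioning either fallback. This largely stands: nothing shows that a fallback was used. But an option already written into the protocol need not be listed as a modification, so the silence does not settle which version was carried out.

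**The threshold and the fallback analysis may be in the full protocol or analysis plan.** This is fair for the numeric minimum and for model details. The collapse to one camp per arm, however, is a rule this article states, and it is the rule that needs correcting.

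**The article already steps down its claims.** It relabels the fallback data as comparative cross-sectional and reports everything as observational. It also records other agencies' relief, security developments and disease outbreaks. These help interpretation but supply no between-camp error term, and nothing says that the test would be withheld.

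**Stronger readings that the text does not support.**
- A reader might infer that the intervention is wholly confounded with the camp. The fallback has a before and an after in both camps, so stable differences drop out.
- A reader might infer that losing a single camp triggers the drop from 20 camps to 2. Any number judged sufficient stays in the main design.
- A reader might take 18.5% as the general error rate. It holds here only if camp effects are unrelated between surveys. It would also apply to an endline comparison of two camps (design effect 1 + 119 × 0.01 = 2.19), a combination the article does not describe.
- A reader might conclude that neither fallback can give any answer. An endline survey across all camps still supports an observational comparison, and Study design reports only small differences in vulnerability between camps.

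**Conclusion.** The point holds as a conditional design weakness. Under the one-camp fallback, impact on IDDS and the other risk factors could be read only by assuming that both camps would have changed equally without the intervention, and two camps cannot test that. A nominal 5% test that ignores camps would reject a true null between about 5% and 18.5% of the time, with 12% as a mid-range case. This rests on ICC 0.01 from the protocol, on 120 children per camp and survey, and on an unknown stability of camp effects. The article does not say that camps would be ignored in this test, but with one per arm no valid camp-level alternative exists. Bias from vulnerability targeting is not included in these rates.

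The endline-only fallback is a lesser and different problem: replication between camps survives if all camps are surveyed, but a difference between arms cannot be called an impact. Because the surveys are finished, the consequence now lies mainly in how they are analysed and reported.

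**What to change.** 1. Replace the sampling rule: if access is restricted, keep every safely reachable camp in both arms and spread the fixed household sample across them. State the minimum number of camps per arm needed for any between-arm test.
2. If only one camp per arm is surveyed, report the survey descriptively, with no test or claim of impact on IDDS or the other risk factors.
3. If only an endline is available, report the comparison as an observational association, not as an impact estimate.
4. State in the report which version was carried out and how many camps per arm contributed to each survey, and apply items 2 and 3 to the analysis accordingly.

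The surveillance system cannot stand in for the surveys here. It collects anthropometry to detect acute malnutrition, so it gives no inference on IDDS or the other risk factors.

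Items 2 to 4 cost a few sentences and can still be applied. Item 1 needs no extra households, but spreading a sample over more camps costs travel and staff time, which is not trivial where insecurity is the trigger. With fieldwork finished, item 1 mainly corrects the stated rule. The other cost is a weaker claim if a fallback was in fact used.

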### Sample size calculation

Sample size calculations were performed using Stata (StataCorp. 2015. Release 14. College Station, TX: StataCorp LP). For assessing the change in malnutrition risk factors using survey methods, the sample size was estimated to be able to detect a difference of 0.6 units in the mean individual dietary diversity score (IDDS). A positive change of about 2 units in the household diet diversity score was observed in response to a social CTP in Malawi [15]; but other studies had lower changes [16, 17]. There is little data on IDDS change following cash transfers so we decided to power the study to detect a conservative change, assuming a baseline IDDS of 3.0 with a SD of 1.5, with power of 80%, an alpha risk at 0.05, and an intra-cluster correlation coefficient of 0.01. The resulting required sample size was 120 children per arm. Based on previous nutrition survey data we assumed an average of 1.2 children, aged 6–59 month per household, which implies that 200 households will need to be sampled during each data collection period. Based on previous survey experience, we added 20% to allow for non-response leading to a required total sample of 240 households.

To assess malnutrition incidence using the community surveillance system and detect a hazard ratio of 0.5, we assumed, based on operational guidance for caseload estimations, that the proportion of the population under surveillance that would develop GAM during 6 months was 7%, and there would be 20% loss to follow up. Power was set at 80% and the alpha risk at 0.05. This resulted in a total sample size of 1167 children, which equated to a rounded sample of 600 participants per arm. Because data will be obtained from an exhaustive sample of children in both control and intervention clusters, we expect to have a greater sample.

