### Data analyses

Data analysis will be undertaken using Stata. Prevalence estimates at baseline and endline, will be computed using the *svy* commands which allows for the clustering of values. We will test for endline minus baseline difference-in-differences between the study arms using the data collected in the malnutrition risk factor surveys. Analysis of the incidence of acute malnutrition in the trial arms will be performed using Cox Proportional Hazards analysis. All results will be reported according to STROBE recommendations for observational studies [21].

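### The survey's 80% power for 0.6 IDDS units holds for a single two-arm comparison; under the stated difference-in-differences on independent samples it is about 50–60%

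*Protocol article*

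**What the plan says.** All statements are in the protocol article.

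- **Sample size calculation.** The survey component is sized on mean individual dietary diversity score: "the sample size was estimated to be able to detect a difference of 0.6 units in the mean individual dietary diversity score (IDDS"). The score itself enters the calculation as "assuming a baseline IDDS of 3.0 with a SD of 1.5"; the error rates and the clustering enter it as "with power of 80%, an alpha risk at 0.05, and an intra-cluster correlation coefficient of 0.01". The result: "The resulting required sample size was 120 children per arm". At 1.2 children per household this becomes 200 households, "which implies that 200 households will need to be sampled during each data collection period". Then "we added 20% to allow for non-response leading to a required total sample of 240 households".
- **Study design.** There are 10 intervention camps and 10 control camps, allocated without randomisation.
- **Study components.** As the working plan, "the surveys will select independent samples of households from the study clusters at the two periods". A followed cohort is foreseen only if field conditions turn out better than expected, and a single endline survey only if security prevents repeat surveys.
- **Data analyses.** "We will test for endline minus baseline difference-in-differences between the study arms", using the risk-factor survey data.
- **Outcome measures.** Mean IDDS in children aged 6–59 months is one of the two primary outcomes.

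**The concern.** The sample size section names no difference-in-differences variance and no correlation between baseline and endline. Its inputs describe one contrast of two means. The analysis section specifies a contrast of four means, and under the working plan those come from separate household samples, so there is no within-child correlation to offset the noise that the baseline round adds. If 120 per arm was derived for the simpler contrast, the stated 80% does not belong to the stated test. At stake is how a non-significant result on a primary outcome is read: a reader who takes the 80% at face value would give such a result more weight against a 0.6-unit effect than the design supports.

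**Working it through.** **Inputs.** Difference d = 0.6, SD = 1.5, ICC = 0.01, 80% power, alpha 0.05, n = 120 children per arm per round (Sample size calculation); 10 camps per arm (Study design), hence 12 children per camp per round. The article does not say whether alpha is two-sided; two-sided is assumed here.

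**Step 1: reproduce 120 per arm as a single two-arm comparison.**

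- Without clustering: n = 2 × (1.96 + 0.8416)² × (1.5/0.6)² = 98.1, so 99 per arm.
- Design effect at 12 per camp: 1 + (12 − 1) × 0.01 = 1.11.
- SE at n = 120: 1.5 × √(2 × 1.11/120) = 0.2040, and 0.6/0.2040 = 2.94.
- Power: 79.4% (t on 18 df) or 83.7% (normal).
- Solving for n at 80% power with 10 camps per arm gives 108 (normal) or about 122 (t, 18 df).

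So 120 is a sound figure for one comparison at one time point, and the t version is the closer match.

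**Step 2: the difference-in-differences on independent samples.** With four independent sample means,

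SE = SD × √(4D/n),

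where D depends on how camp effects behave between rounds. If they are unrelated between rounds, D = 1.11. If they are fully stable, they cancel within camp and D = 1 − 0.01 = 0.99.

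| n per arm per round | D | SE | 0.6/SE | Power, t (18 df) | Power, normal | Detectable at 80%, t | Detectable at 80%, normal |
|---|---|---|---|---|---|---|---|
| 120 | 0.99 | 0.2725 | 2.20 | 54.9% | 59.6% | 0.81 | 0.76 |
| 120 | 1.11 | 0.2885 | 2.08 | 50.3% | 54.8% | 0.85 | 0.81 |
| 144 | 0.99 | 0.2487 | 2.41 | 62.6% | 67.4% | 0.74 | 0.70 |
| 144 | 1.134 | 0.2662 | 2.25 | 56.9% | 61.6% | 0.79 | 0.75 |

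The 144 rows are full response: 240 households × 1.2 / 2 arms = 144 children per arm, 14.4 per camp, design effect 1 + 13.4 × 0.01 = 1.134. The detectable difference is SE × 2.80 (normal) or SE × 2.96 (t, 18 df).

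**Step 3: could 120 already allow for the difference-in-differences?** No. For 80% power at 0.6 units the smallest requirement (normal, camp effects cancelling) is 2 × 98.1 × 0.99 = 194.3 children per arm per round. With D rising with camp size it is about 242. On the t basis the range is about 218–279.

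**Step 4: non-response.** If 20% of the 240 households do not respond, 240 × 0.8 × 1.2 = 230.4 children remain, against 240 required. For the single comparison this lowers power from 79.4% to 78.0% (t) or from 83.7% to 82.3% (normal).

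**The case against.** Several defences deserve an answer.

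- **The figure was meant for an endline comparison.** At 120 per arm with 10 camps per arm, that comparison has about the stated power. But the article keeps a single endline survey for bad security conditions only, frames the sizing as assessing change, and specifies a difference-in-differences. In a trial allocated on vulnerability, the endline contrast is also not an equivalent substitute.
- **SD 1.5 might be the SD of a change.** The text attaches it to the baseline score, and independent samples contain no within-child change.
- **A cohort may have been followed.** This stands as a limit on the point. Assuming a within-child correlation of 0.5, which is not in the article, normal-approximation power would be about 84–87%; at an assumed 0.3 it would be about 70–74%. The article reports that the surveys are complete but not which design was used.
- **Covariate adjustment could reduce residual variance.** It could, and its details may sit in an analysis plan not shown. The article gives nothing from which to size the gain.
- **The non-response step is a convention.** Largely right. Adding 20% to 200 covers 16.7% non-response, and the text does not say that 20% of households will fail to respond. A reader might infer an arithmetic error that undermines the sample; a loss of about 1.5 points of power does not support that.

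A reader might also infer that the authors intended an endline-only comparison, or relied on an unstated correlation. The article gives no such basis, so neither should be attributed to them.

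**Conclusion.** The power statement for IDDS is wrong as written for the base plan of independent household samples. For 0.6 units, the difference-in-differences with 120 children per arm per round has about 50–55% power (t, 18 df) or 55–60% (normal), against the stated 80%; the width of each range reflects whether stable camp effects cancel. The result does not hinge on the ICC: with no clustering at all, power is 54.5% (t) or 59.1% (normal). It rests on two-sided alpha, SD 1.5 in every arm and round, and 10 camps per arm.

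Three stronger readings go too far. The 120 is not a slip in calculation; it is right for a different contrast. The shortfall is not a property of every design the article allows: it does not carry over to the single endline survey with 10 camps per arm, and under a cohort it depends on a correlation the article does not state. Nor does the article say that a null IDDS result will be taken as proof of no effect; that is a risk in interpretation, not a stated rule. The mismatch costs precision and does not bias the estimate.

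**What to change.** 1. Restate the IDDS power and detectable difference for the difference-in-differences, on one labelled method. On the t basis that best reproduces 120, this reads: about 50–55% power for 0.6 units, and 80% power for about 0.81–0.85 units. On the normal basis: about 55–60%, and about 0.76–0.81 units.
2. Say that 80% power for 0.6 units holds only for a single-time-point comparison of the arms with 10 camps per arm.
3. Interpret the IDDS result by its confidence interval, so that a non-significant difference is not taken to exclude 0.6 units unless the interval does.
4. If the baseline sample was in fact followed up, state that and give power for the cohort analysis with the within-child correlation named as an assumption.
5. Minor: if 20% non-response is what was meant, state that 240 households are expected to yield about 230 children per round.

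The surveys are already complete (Study status), so the sample cannot be changed. The cost is wording only, with a less favourable power statement and no new data.

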**Methods/design:**

A non-randomised, cluster-controlled trial will assess the impact of an unconditional cash transfer of US$84 per month for 5 months, a single non-food items kit, and free piped water on the risk of acute malnutrition in children, aged 6–59 months. The study will take place in camps for internally displaced persons (IDP) in peri-urban Mogadishu, Somalia.

A cluster will consist of one IDP camp and 10 camps will be allocated to receive the intervention based on vulnerability targeting criteria. The control camps will then be selected from the same geographical area. Needs assessment data indicates small differences in vulnerability between camps.

In each trial arm, 120 households will be randomly sampled and two detailed household surveys will be implemented at baseline and 3 months after the initiation of the cash transfer. The survey questionnaire will cover risk factors for malnutrition including household expenditure, assets, food security, diet diversity, coping strategies, morbidity, WASH, and access to health care. A community surveillance system will collect monthly mid-upper arm circumference measurements from all children aged 6–59 months in the study clusters to assess the incidence of acute malnutrition over the duration of the intervention. Process evaluation data will be compiled from routine quantitative programme data and primary qualitative data collected using key informant interviews and focus group discussions.

The UK Department for International Development will provide funding for this study. The European Civil Protection and Humanitarian Aid Operations will fund the intervention. Concern Worldwide will implement the intervention as part of their humanitarian programming.

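### The survey's 240 households secure 120 children per arm only if non-response is at most 16.7%; at 20% non-response they yield about 115

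*Protocol article*

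**What the plan says.** The Sample size calculation section of the Protocol article sizes the household surveys on mean individual dietary diversity score (IDDS), one of the two primary outcomes. It arrives at 120 children per arm. Taking 1.2 eligible children per household, it needs 200 households across both arms in each survey round. It then says: "we added 20% to allow for non-response leading to a required total sample of 240 households". The 20% is attributed to earlier survey experience. The abstract restates the result by arm: "In each trial arm, 120 households will be randomly sampled".

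The next paragraph of the same section sizes the surveillance component for the other primary outcome. It assumes that 7% of children develop acute malnutrition and that 20% are lost to follow-up, and reports: "This resulted in a total sample size of 1167 children".

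**The concern.** An allowance for non-response should leave the required number after the expected fraction has dropped out. If a fraction d does not respond, the number to approach is N/(1 - d). Multiplying by (1 + d) gives a smaller number and leaves a shortfall when d is the true rate. The survey calculation multiplies. The surveillance calculation, one paragraph later, divides.

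At stake is whether the stated sample for a primary outcome meets its own target of 120 children per arm. A reader who sees 20% added for non-response will probably take 240 households as protection against 20% non-response, and they do not give that protection.

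**Working it through.** **Inputs** (Protocol article; Sample size calculation unless noted)

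- Difference in mean IDDS: 0.6 units.
- Other survey assumptions: "assuming a baseline IDDS of 3.0 with a SD of 1.5, with power of 80%, an alpha risk at 0.05", with "an intra-cluster correlation coefficient of 0.01".
- Clusters (Study design): "the intervention arm will include 10 IDP camps selected to receive the intervention"; "The control arm will include another 10 IDP camps".
- Required children: 120 per arm, 240 in total.
- Children per household: 1.2.
- Allowance: 20% added. No expected non-response rate is given separately.
- Assumed here because not stated: a two-sided test, equal cluster sizes, and power for a single two-arm comparison at one time point.

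**1. Reproducing the stated 240**

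- Households before the allowance: 2 x 120 / 1.2 = 200.
- After adding 20%: 200 x 1.2 = 240, or 120 per arm. This matches the plan exactly.

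**2. What 240 households cover**

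- Largest non-response that still leaves 200 households: 1 - 200/240 = 16.7%.
- At 20% non-response: 240 x 0.8 = 192 households; 192 x 1.2 = 230.4 children; 115.2 per arm.
- Shortfall: 120 - 115.2 = 4.8 children per arm; 4.8/120 = 4%.

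**3. The figure if 20% is the expected rate**

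- 200 / 0.8 = 250 households, or 125 per arm.
- Check: 250 x 0.8 x 1.2 = 240 children, or 120 per arm.

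**4. How the surveillance calculation treats its 20%**

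- Events by the Schoenfeld formula for a hazard ratio of 0.5: (1.96 + 0.842)^2 / (0.25 x ln(0.5)^2) = 65.35.
- Children before loss: 65.35 / 0.07 = 933.5.
- Divided by 0.8: 1167, the stated total. Multiplied by 1.2 it would have been 1120.

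The surveillance allowance was therefore made by division.

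**5. Effect on power for IDDS**

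With 10 clusters per arm and m children per cluster, SE = 1.5 x sqrt(2 x (1 + (m - 1) x 0.01) / (10m)).

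| Children per arm | m | Power, normal | Power, t on 18 df |
|---|---|---|---|
| 120 | 12 | 83.7% | 79.4% |
| 115.2 | 11.52 | 82.3% | 78.0% |

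For example, at m = 12 the SE is 1.5 x sqrt(2 x 1.11 / 120) = 0.204, and 0.6/0.204 = 2.94. The loss is about 1.4 points by either method. The normal approximation needs 11 children per cluster (110 per arm) for 80% power.

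**The case against.** The strongest reply is that the sentence is correct as written. It says that 20% was added, and 200 plus 20% is 240. It gives the size of an increase, not a rate of non-response. The surveillance text, by contrast, does give a rate of loss, so each figure follows its own wording. The two quantities also differ: loss during cohort follow-up is not household non-response at a survey. This stands. A reader might infer that 240 is a plain arithmetic error, or that 240 households cannot deliver 120 children per arm. The document supports neither. With non-response up to 16.7% the target is met, and the earlier survey experience behind the 20% is not shown.

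The reply does not remove the point. What earlier surveys supply is most naturally a non-response rate; the parallel 20% in the same section is a loss rate; and 240 is presented as the number required. Even on the literal reading, the section leaves the rate it protects against unstated, and 16.7% is not the figure most readers would take from it.

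A second reply is that 1.2 children per household is itself rounded. At 1.25, 192 responding households give 192 x 1.25 = 240 children, which is the full target. That is true, but rounding works in both directions: at 1.15 they give 192 x 1.15 = 220.8, or 110.4 per arm. It shows that the shortfall is small relative to the precision of the inputs, but it does not settle what the allowance covers.

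A third reply is that the effect on power is negligible. This largely stands. By the normal approximation, 115 per arm still exceeds 80%. By the t calculation, 120 per arm is already marginally below 80%, so the shortfall does not turn an adequate design into an inadequate one.

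**Conclusion.** The concern holds in conditional form and is minor. The step from 200 to 240 households keeps 120 children per arm only while non-response is at most 16.7%. If 20% is the expected non-response rate, the yield is about 115 children per arm and the matching requirement is 250 households, 10 more than stated.

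The conclusion rests on the plan's own 120 children per arm and 1.2 children per household. The shortfall rests additionally on reading the 20% as a rate, which is natural but not stated outright. The power figures depend on the assumptions listed with the inputs.

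Two further inferences should be resisted. The shortfall does not show that the survey is materially underpowered, since the change is about 1.4 points. Nor is the abstract wrong: it gives the number of households to be sampled per arm, agrees with 240 in total, and makes no claim about responders.

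**What to change.** The Study status section reports the risk factor surveys as completed, so raising the target to 250 households is no longer a practical option. Keep 240 and correct the sentence in the Sample size calculation section in one of two ways: say that 240 households allow for up to 16.7% non-response, or, if 20% was the rate expected, say that 240 households yield about 115 children per arm at that rate and that 250 (125 per arm) would have been needed for 120. Leave the abstract as it is.

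The cost is one sentence. It needs no new data and no change of design or analysis, and it makes the stated figure slightly less favourable.
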